| Data/ Statistical Analysis **Prognostic modelling**  ***Aim 1 – prognostic model derivation (primary analysis)***  Where feasible and appropriate, flexible parametric survival models will be derived in the CPRD GOLD for each outcome separately. Baseline survival over time will be estimated using the Royston-Parmar approach of restricted cubic splines on the cumulative log hazard scale. In contrast to Cox regression, this allows a smoothed estimate of the baseline survival function to be derived, and the time period of prediction to be varied, facilitating individualised risk prediction. For the primary analysis, a 10-year period of prediction will be considered. Further sensitivity analyses will be conducted examining a 5-year period. Where insufficient data are available, or modelling procedures become prohibitively complex (computationally), simpler approaches such as Cox regression will be considered.  Each drug class (prescribed in the 12 months prior to the index date) will be entered into the model as a binary variable to allow for multiple treatments to be considered in each model. Where appropriate, models will be constructed with all other variables entered as continuous (not categorised) variables, and potential non-linear trends will be examined. Transformations or fractional polynomials will be used if non-linear trends are detected. Where hazard ratios are not proportional, interactions of effects with time will be included. Further interaction terms, identified in an accompanying systematic review, accounting for treatment effects which differ across specific populations may be included. Where appropriate, models will be reduced and candidate predictors selected for inclusion based on p values of association. Time since cohort entry will be used as the underlying time function in each survival model.  In a further analysis, we will extend the modelling process as described above to account for competing risk of death from other causes. This will produce a model that predicts the risk of adverse events from cardiovascular treatment over time, in the real world where individuals might die from other causes and thus prevent cardiovascular treatment adverse events from occurring. We will again use a flexible parametric modelling framework to estimate the sub-distribution hazard and cause-specific cumulative incidence functions.^45^  Missing data will be handled, under a missing at random assumption, using multiple imputation (see below) followed by Rubin’s rules to combine parameter estimates across studies.  Where feasible and appropriate, each model will be internally validated using the bootstrap method, to allow optimism-adjusted estimates of calibration and discrimination performance to be obtained. Adjustment for overfitting will be undertaken using a uniform shrinkage factor identified from bootstrapping, followed by re-estimation of the cumulative baseline sub-distribution hazard function (and thus baseline cumulative incidence function) to maintain overall calibration between observed and predicted risks. Given the large sample size, overfitting is likely to be small (see sample size calculation above). If bootstrapping is computationally infeasible due to the large sample size, then a smaller random sample of the population will be used or alternative internal validation methods employed such as cross validation.  ***Aim 2 – prognostic model validation***  External model validation will be undertaken using data from CPRD Aurum. The accuracy of risk predictions from each model will be assessed with calibration plots and 5 and 10 years, calibration measures (slope, E/O statistics), measures of overall fit (using pseudo-R^2^ estimates) and discrimination measures (C-statistics and D-statistics).  ***Aim 3 – causal inference analysis***  For most of the outcomes described in this proposal, the association and magnitude of effect with treatment is not well defined in randomised controlled trials. We will therefore undertake causal inference work to examine whether modification of treatment could have an important impact on the risk of adverse events using two causal inference methods: propensity score matching and instrumental variable analysis.  For the propensity score analysis, eligible patients will be matched 1:1 at the index date using propensity scores, which indicate the likelihood a patient will be prescribed treatment on the basis of their known (pre-treatment) characteristics and other known information which might influence the decision to treat. Predictors of preventative drug prescription will be explored in a logistic regression model. Matched patients will be compared using the Cox proportional hazards models, but hazard ratios will only be adjusted by factors unbalanced at baseline which are not already included in the propensity score model. Time since cohort entry will be used as the underlying time function in each model.  For the instrumental variable analysis, GP’s previous antihypertensive prescribing preferences will be used as an instrument to predict the likelihood of actual treatment. Risk of adverse events will be estimated in patients attending a GP considered a high prescriber of preventative medication and compared to those attending a GP considered a low prescriber. If the results from the propensity score matching suffer from unmeasured confounding, they will differ from those of the instrumental analysis. If this is the case, these models will be refined with additional factors to achieve better adjustment and matching. Where all approaches provide similar results, we can be more confident that the findings are accurate and reliable.^46^  A similar approach will be applied to secondary outcomes, for example, memory loss which has been hypothesised as being linked with statins^47^ and is a concern of many patients in practice, but there is no evidence to support this association from trials.^48^ We recognise that the evidence base may change for some outcomes over the next few years, and so the need to test the associations between treatment and certain outcomes may change.  *Subgroup and sensitivity analyses*  Where possible and appropriate, analyses of treatment associations will be examined in subgroups of the population. These will include age, sex, baseline blood pressure and cardiovascular risk, by drug type/dose/intensity and past medical history. Subgroup definitions will be agreed by expert opinion or taken from an accompanying systematic review of previous trials, examining the same topic.  Sensitivity analyses will be undertaken examining risk models for outcomes defined according to both hospital and primary care records. We will also explore the impact of our definition of myopathy and muscle pain, focussing on formal diagnostic codes for myopathy only. Models utilising a 5-year follow-up will be examined as a further sensitivity analysis. The primary analyses will examine the association between treatment and outcomes, assuming treatments are not altered or modified in the future. Where possible, sensitivity analyses will examine treatment entered as time varying covariates, and censor patients who have treatments removed or switched following the index date. |

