| Limitations of the study design, data sources, and analytic methods This study focuses on potential harms from adverse events associated with preventative treatments for cardiovascular disease. Such outcomes may be less well recorded in routine electronic health records. For example, initial scoping work suggests the rate of falls documented in the CPRD is between 0.06-0.34% per 1000 person-months. These incidence rates may be less than those reported in smaller previous studies (0.15-6.40% per 1000 person-months) using different definitions, captured via detailed questionnaires and follow-up.^49-52^ Incidence rates are likely to be higher when linked data from HES and ONS are available.^53^ Missing data on certain outcomes may reduce the accuracy of the prognostic models, but should not bias the results provided the data are missing at random and not affected by whether patients are prescribed treatment. To minimise the risk of reporting bias, outcomes in the primary analysis will be defined according to hospital admissions documented in the HES or ONS.  The causal inference work will use an observational cohort design, and as such, there is an inherent selection bias of patients in both exposure and control groups. The impact of this bias will be limited by propensity score methods used to control for confounding, but this approach assumes that all confounding factors are measured and accounted for within the analysis. In the present study, we will examine the validity of this assumption by 1) using an instrumental variable (GP prescriber preference) and examining the association with the outcomes of interest and 2) by studying the impact of treatment on positive and negative controls: hospitalisation and/or death from cardiovascular disease and bowel cancer/COPD. We will conclude the assumption has been met if high GP prescribers have a similar association with outcomes and the treatment itself and treatment is shown to be associated with the positive control, but not the negative control.  *Strategy for dealing with potential errors resulting from multiple testing*  This study will examine multiple outcomes across 3 exposure variables. To avoid potential errors arising from multiple testing, a primary outcome has been clearly defined for each exposure variable. Secondary outcomes are also pre-specified. The primary outcome will be given priority in the final analysis write-up and any related reports and presentations.  Primary and secondary outcomes will be defined using data from Basic inpatient HES and ONS. Sensitivity analyses will explore analyses defining these outcomes using the above sources and read-coded primary care data. The accuracy of such outcome data has been examined previously in patients with acute myocardial infarction and whilst recording of risk factor and co-morbid information was consistent across primary care, hospital admissions and disease registry records, the crude incidence of acute myocardial infarction was underestimated by up to 50% if only one data source was used, compared with using all three sources.^53^ The use of linked CPRD data will ensure outcome data are ascertained accurately. |

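### The instrumental-variable check names only an antihypertensive preference for three drug groups, and its similarity rule compares a diluted prescriber contrast with a treatment effect

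*Protocol*

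**What the plan says.** All references are to Part 2 of the protocol.

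- **Data/Statistical Analysis, Aim 3**, names the instrument: the GP's "previous antihypertensive prescribing preferences will be used as an instrument to predict the likelihood of actual treatment". Amendment 3 reprints this paragraph.
- The next sentence gives the contrast and changes the label: "Risk of adverse events will be estimated in patients attending a GP considered a high prescriber of preventative medication and compared to those" in the care of a low prescriber.
- The same paragraph says that if the propensity-score results are affected by unmeasured confounding, "they will differ from those of the instrumental analysis". In that event, "these models will be refined with additional factors to achieve better adjustment and matching".
- **Limitations** describes the check with no drug class, as "using an instrumental variable (GP prescriber preference) and examining the association with the outcomes of interest". It sets the rule: "We will conclude the assumption has been met if high GP prescribers have a similar association with outcomes and the treatment itself". The same rule also requires the positive and negative control outcomes to behave as expected.
- **Sample size considerations** gives one calculation for propensity-score matching and IV analysis together: a 10% increase, 0.5% per year in the unexposed, 90% power, alpha 0.05, hence 4,634 events and 88,380 patients.

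**The concern.** There are two problems.

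**Instrument.** Three labels are in use: antihypertensive preference, prescribing of preventative drugs generally, and prescriber preference with no class. None measures preference for statins or for antiplatelets. The narrow label leaves relevance to those two drug groups unsupported. The broad label moves all three exposures together, so any effect of a co-prescribed class on the outcome would breach the exclusion restriction. Intracerebral haemorrhage is listed as an outcome for both statins and antiplatelets.

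**Contrast.** Comparing outcomes between patients of high and low prescribers is a reduced-form contrast. It equals the treatment effect only if treatment has no effect, or if every patient of a high prescriber is treated and no patient of a low prescriber is. The Limitations rule asks for similarity all the same.

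At stake is the reading of the matched results. A sound estimate could be judged confounded and its model altered, while an estimate biased towards 1 could be accepted.

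**Working it through.** **1. The plan's own figure.** Freedman's formula with HR 1.10, two-sided alpha 0.05 and 90% power:

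(1.960 + 1.282)² × ((1 + 1.10)/(1 − 1.10))² = 10.507 × 441 ≈ 4,634 events. This matches.

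Taking 0.5% per year over 10 years as 5%, survival is 0.95 in the unexposed and 0.95^1.1 = 0.94514 in the exposed. The mean event probability is (0.05 + 0.05486)/2 = 0.05243, and 4,634/0.05243 ≈ 88,380 patients. This matches too. The 10-year horizon is inferred: on the same method, 5 years gives 176,642 and 7 years gives 126,208. The stated figures are therefore for treated versus untreated patients.

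**2. What the prescriber contrast would show.** Assume a valid instrument, no confounding and a true HR of 1.10. Let q be the share treated and δ = q_high − q_low. The documents do not give δ, so a range is used, centred on 50% treated.

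S(q) = (1 − q) × 0.95 + q × 0.95^1.1

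Prescriber HR = ln S(q_high) / ln S(q_low)

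For δ = 0.2: S(0.6) = 0.947084 and S(0.4) = 0.948056. The prescriber HR is (−0.054368)/(−0.053342) = 1.019.

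| δ | Prescriber HR | Events for 90% power | Power with 4,634 events |
|---|---|---|---|
| 0.1 | 1.010 | 463,324 | 5% |
| 0.2 | 1.019 | 115,832 | 10% |
| 0.3 | 1.029 | 51,481 | 16% |
| 0.4 | 1.039 | 28,959 | 25% |
| 0.5 | 1.049 | 18,534 | 37% |
| 1.0 | 1.100 | 4,634 | 90% |

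The required events rise by about 1/δ². Events and power assume prescriber groups of equal size.

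**3. Scaling removes the dilution.** The Wald estimate is the risk difference divided by δ. At δ = 0.2 it is (0.948056 − 0.947084)/0.2 = 0.00486. The true 10-year risk difference is 0.95 − 0.94514 = 0.00486. The same value is recovered at every δ in the table.

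**4. The rule applied.** At δ = 0.2, a correct matched HR of 1.10 is set against 1.019 and looks discordant. A matched HR biased from 1.10 down to about 1.02 looks concordant.

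**5. Statins and antiplatelets.** Suppose antihypertensive preference shifts their uptake by none to half of δ = 0.2 (assumed). The contrast expected for a true HR of 1.10 is then 1.000 to 1.010.

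**6. What the unscaled contrast can still do.** With the 216,000 falls in the feasibility counts, power to distinguish the diluted HR from 1 is 60% at δ = 0.1 and 99% at δ = 0.2. With the 1,200 intracranial haemorrhages it is 4% to 10% for δ of 0.1 to 0.4.

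**The case against.** A reader might infer more than the documents support, in four ways.

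- **That antihypertensive preference is fixed as the instrument for all three drug groups.** No sentence says so. The labels conflict, the narrow one may be a slip, and Amendment 3 reprints the paragraph rather than confirming it independently. What stands is that no label is specific to statins or antiplatelets.
- **That no first stage is planned.** Predicting the likelihood of treatment implies one, and estimator detail may sit in an analysis plan not shown here. A scaled estimate is not ruled out, only not described. But the protocol itself fixes the similarity rule, and that rule uses the high-prescriber association, so this is more than detail left for later.
- **That the check is worthless even for antihypertensives.** With a valid instrument, the reduced form is a valid test of no effect and of direction, and it is well powered for falls at δ = 0.2. If treatment has no effect, both contrasts equal 1 and the rule works. It fails as a comparison of size.
- **That the exclusion restriction is certainly broken, or that the contrast says nothing about statins and antiplatelets.** Both depend on cross-class effects and on how far preferences track each other, which the documents do not give. Other prescribed medications are a listed covariate.

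It is also fair that similarity has no numerical threshold, so a misreading is likely rather than certain. The control outcomes must agree as well before the assumption is accepted, and Amendment 2 adds multivariable and propensity-adjusted analyses.

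**Conclusion.** The concern holds in this form. The instrument is labelled inconsistently and is never specific to statins or antiplatelets. The stated rule sets an unscaled prescriber contrast beside a treatment effect. With a true HR of 1.10 and no confounding, that contrast is about 1.01 to 1.04 for uptake differences of 10 to 40 points, and it reaches 1.10 only at 100 points. These figures rest on an assumed uptake difference centred on 50%, a valid instrument and the inferred 10-year horizon. The direction of the error does not depend on the exact uptake difference: whenever treatment has an effect and the difference is below 100 points, similarity is the wrong criterion. This should be fixed. It falls short of a critical flaw because the IV analysis is one of several checks, alongside positive and negative controls.

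**What to change.** 1. Reconcile Aim 3, Limitations and Amendment 3 on one definition: for each cohort, the GP's or practice's preference for that cohort's own drug group.
2. Adjust for the GP's preference for the other two groups. Do not condition on patients' later co-prescription, which the GP's general preference may itself influence and which could introduce bias.
3. Report first-stage strength, including the uptake difference, for each drug group.
4. Estimate a first-stage-scaled effect, for example by two-stage least squares on risk, with standard errors clustered on GP or practice.
5. Reword the Limitations rule, and the matching sentence in Aim 3, to compare that estimate and its interval with the propensity-score estimate on the same scale. State that the two may differ because they apply to different patients: those whose treatment depends on the prescriber's preference, and the matched patients. A difference is then not in itself proof of confounding.

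The cost is protocol wording and modest programming. The prescribing records are needed anyway to define exposure. The IV intervals will be wider, and for intracranial haemorrhage probably too wide to discriminate.

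### The GP-preference instrument is used to test the propensity analysis, but no check of the instrument itself is specified and the decision rules do not allow for its being invalid

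*Protocol*

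**What the plan says.** The instrument is set out in Data/Statistical Analysis, Aim 3: "GP’s previous antihypertensive prescribing preferences will be used as an instrument to predict the likelihood of actual treatment". The comparison follows: "Risk of adverse events will be estimated in patients attending a GP considered a high prescriber of preventative medication and compared to those attending" (the other group being patients of low prescribers). Amendment 3 repeats this paragraph unchanged.

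Two rules then fix how the result is used.

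- **Disagreement** (Aim 3): "If the results from the propensity score matching suffer from unmeasured confounding, they will differ from those of the instrumental analysis". The stated response is that "these models will be refined with additional factors to achieve better adjustment and matching". The mention of adjustment and matching points to the propensity models.
- **Agreement** (Limitations of the study design): "We will conclude the assumption has been met if high GP prescribers have a similar association with outcomes and the treatment itself". The same sentence also requires an association of treatment with the positive control and none with the negative control.

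The control outcomes are described in Limitations as a check made "by studying the impact of treatment on positive and negative controls", and Plan for addressing confounding describes them in the same way.

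Covariate handling is stated for the other Aim 3 methods. In the propensity-matched analysis, "hazard ratios will only be adjusted by factors unbalanced at baseline which are not already included in the propensity score model". Amendment 2 adds a multivariable Cox analysis adjusted for pre-specified confounders. There is no corresponding sentence for the IV analysis.

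**The concern.** A preference instrument is informative only if patients of high- and low-prescribing GPs have comparable outcome risk apart from the treatment they receive. A GP with older, frailer or more hypertensive patients may prescribe more because of those patients, and the same characteristics raise the risk of falls and bleeding. The protocol states the matching requirement for propensity methods, that all confounders are measured. It does not state the requirement for the instrument.

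This matters because the IV result decides what happens next. If patient mix biases the IV contrast, a sound propensity result can be declared confounded and reworked towards a faulty benchmark. If patient mix pushes both analyses the same way, their agreement counts towards accepting a biased propensity result. Testing bowel cancer/COPD and cardiovascular disease against treatment says nothing directly about whether the instrument is related to patient risk.

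**Working it through.** **1. The plan's own benchmark.** Sample size considerations gives a 10% rate increase, 90% power, alpha 0.05, 4,634 events and 88,380 patients. Freedman's formula, two-sided:

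events = (1.960 + 1.282)² × ((1.10 + 1)/(1.10 − 1))² = 10.507 × 441 ≈ 4,634, as stated.

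For the number of patients, take a 10-year horizon. This is inferred: it matches the primary prediction period but is not stated with the calculation. Control risk is 10 × 0.5% = 5.0%, treated risk is 1 − 0.95^1.1 = 5.486%, and the mean is 5.243%. Then 4,634/0.05243 ≈ 88,384, against 88,380 stated. The figure reproduces. It refers to treated versus untreated patients.

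**2. What is specified for each Aim 3 method.**

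| Method | Covariates | Balance or validity check |
|---|---|---|
| Propensity score | Pre-treatment characteristics in the score; unbalanced factors adjusted | Baseline imbalance considered; IV comparison; control outcomes |
| Multivariable (Amendment 2) | Pre-specified confounders | Comparison across methods; control outcomes |
| IV | None specified | None specified for the instrument |

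**3. Reading the rules.** Taken literally, the disagreement sentence says that confounding in the propensity analysis implies a difference. The response treats the converse as true as well: a difference leads to refinement. A difference has at least one other cause, an instrument related to patient risk, and neither rule mentions it.

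**4. Illustration: age gap.** No input here comes from the documents. Assume no drug effect, a hazard rising 5% to 10% per year of age, and patients of high prescribers 1 or 2 years older on average. The unscaled contrast is (hazard ratio per year)^(age gap):

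| Age gap | 5% per year | 10% per year |
|---|---|---|
| 0 years | 1.00 | 1.00 |
| 1 year | 1.05 | 1.10 |
| 2 years | 1.05² = 1.10 | 1.10² = 1.21 |

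**5. Illustration: share of sicker patients.** Also assumed: no drug effect, and sicker patients with k times the event rate forming a share a of high-prescriber lists and b of low-prescriber lists. The ratio is (a·k + 1 − a)/(b·k + 1 − b).

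- 52/48 split, k = 2: 1.52/1.48 = 1.03
- 55/45 split, k = 3: 2.10/1.90 = 1.11
- 60/40 split, k = 5: 3.40/2.60 = 1.31

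**6. Scale.** A contrast between GP groups is diluted relative to a treated-versus-untreated ratio. Assume 30% average prescribing and a true ratio of 1.10. A 10-point prescribing gap gives (1 + 0.1 × 0.35)/(1 + 0.1 × 0.25) = 1.01. A 50-point gap gives (1 + 0.1 × 0.55)/(1 + 0.1 × 0.05) = 1.05. So an unscaled contrast can also differ from the propensity hazard ratio with no confounding in either analysis.

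**The case against.** The strongest reply is that silence is not a statement. The IV outline is short and nowhere says that the analysis is crude. The covariate set, the measure of preference and the high/low cut-off are details that an analysis plan may hold. Exposures, Outcomes and Covariates lists predictors of outcome and/or treatment, and Plans for addressing missing data speaks of covariates in the causal inference modelling without excluding the IV model. Aim 3 is limited to new users over 40 at a defined index date, with blood pressure and cholesterol exclusions, which narrows case mix. The IV is also not the only safeguard: the control outcomes must behave as expected, and Amendment 2 adds further analyses.

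Much of this stands. A reader might infer that the IV analysis is unadjusted by design, that a GP with sicker patients will be classed as a high prescriber, or that case mix will be reported as drug harm. The documents support none of these. The first two turn an omission into a rule. As for the third, Limitations uses the IV to examine the propensity assumption.

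The reply does not reach the decision rules. They are written into the protocol, and they give the IV result a fixed meaning without requiring evidence that the instrument is valid. Eligibility limits reduce variation in age and frailty but do not remove it, and the control outcomes are directed at treatment. It is also fair to say that adding factors to a propensity model has not been shown to damage a sound result. The objection to that step is that it may be triggered by, and steered towards, a faulty comparison.

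**Conclusion.** The point holds as a defect in the decision rules, combined with the absence of any specified check on the instrument. Following the text, the investigators could attribute to the propensity analysis a difference that comes from patient mix between GPs. They could also count an agreement as support when both analyses are biased the same way and the negative control does not reveal it.

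The size is unknown from the documents. The illustrative 1.05 to 1.21 rests wholly on the assumed age gap and hazard gradient, and with no gap there is no bias. It shows only that modest case-mix differences could give a contrast comparable in size with the 10% effect the study is sized for. The two are not strictly like for like, since the 10% is a treated-versus-untreated effect.

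A reader might go on to divide the log contrast by an assumed difference in treatment between GP groups and arrive at much larger hazard ratios. The protocol describes no such rescaling and gives no first-stage difference, so those figures are not supported.

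**What to change.** 1. Enter the baseline covariates from Exposures, Outcomes and Covariates (those known at the index date) in both the treatment and the outcome stage of the IV model. Alternatively, standardise each GP's preference for case mix among eligible patients.
2. Tabulate covariate balance across instrument levels, with the criterion for imbalance set in advance.
3. Run the control outcomes against the instrument as well as against treatment. The negative control is the informative one here, because an instrument that moves treatment should also move the positive control.
4. Amend the disagreement rule in Aim 3 so that a propensity/IV difference may also reflect an invalid instrument. Amend Limitations in the same sense, and do not apply the agreement rules where measured covariates remain unbalanced across instrument levels.

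Comparing GPs within the same practice is optional. It needs identifiers for individual GPs, which the documents do not show to be available.

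The cost is modest: the covariates are already planned for the other analyses, and the extra work is some modelling and tables. IV confidence intervals may widen, particularly if standardised preference varies less between GPs.
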